**Fig. 2 Fig2:**
[figure not shown]
Study protocol of the incremental PEEP titration procedure determined by Cdyn in patients of the Group I

### Outcome assessment

The primary endpoint of this trial will be the incidence of POD within 3 days after surgery. POD will be determined by an independent researcher who will not know the group assignment using CAM [17]. The investigator will participate in a training session including symptoms and diagnosis of delirium and will not know the group assignment. The researcher will assess POD once daily, between 6: 00 am to 8: 00 am. Four key delirium characteristics consist of CAM diagnostic criteria: (1) acute onset and disease fluctuations, (2) inattention, (3) changes in consciousness, and (4) disordered thinking. Delirium will be defined as the presence of (1) and (2), accompanied by (3) or (4) or both [7].

The secondary outcomes will include perioperative rSO_2_ measurement, arterial blood gases, respiratory variables, and plasma concentrations of interleukin (IL)-1β, IL-6, and NSE. The baseline rSO_2_ will be obtained within 2 minutes before anesthesia induction and averaged. Additionally, intraoperative rSO_2_ values will be continuously measured and recorded using a cerebral oximeter at the following timepoint: T_0_: after entering the operating room; T_1_: 5 minutes after starting mechanical ventilation in the supine position; T_2_: 60 minutes after turning over; and T_3_: 5 minutes after taking in the supine position. The serum concentrations of interleukin (IL)-1β, IL-6, and NSE will be determined by ELISA kits. We will collect the blood samples 15 minutes before anesthesia induction (T_0_) and postoperative day 1.

Arterial blood gases will be measured at T_1_ to T_4_ (after breathing air in PACU for 20 minutes). Respiratory variables including P_ET_CO_2_, PEEP, P_peak_, mean airway pressure (P_mean_), Cdyn, PaO_2_/FiO_2_, A-aDO_2_, V_D_/V_T,_ and Qs/Qt will be recorded at T_1_ to T_3_. Each patient will receive two ultrasound examinations at T_1_ and T_4_. And lung ultrasound scans will be performed by an experienced anesthetist who will not know the group allocations. As described previously [18, 19], each hemithorax will be alienated into 6 quadrants and each region will be assigned a score of 0 to 3 according to the different signs of B-line, subpleural consolidation and pleural line under ultrasound scan. The LUS will be calculated to quantitatively assess the aeration loss by adding all scores up.

Postoperative VAS scores will be checked by the ward doctors who will not be involved in this study. When the VAS score is>3 points, participants will receive intravenous Flubiprofen infusion with the dose of 50 mg. The analgesic drug consumption will also be recorded.

Parameters calculating will use formulas below:

$${\mathrm V}_{\mathrm D}/{\mathrm V}_{\mathrm T}=\;(\mathrm{PaCO}2-\;{\mathrm P}_{\mathrm{ET}}{\mathrm{CO}}_2)/{\mathrm{PaCO}}_2$$

$$\mathrm{Qs}/\mathrm{Qt}\;=\;(\mathrm{PA}-{\mathrm{aDO}}_2\times0.0031)\;\div\;(\mathrm{PA}-{\mathrm{DO}}_2\times\;0.0031\;+\;5)$$

$$\mathrm{PA}-\mathrm{aDO}2=\;\lbrack{\mathrm{FiO}}_2\times\;({\mathrm P}_{\mathrm B}-\;{\mathrm P}_{\mathrm H2\mathrm O})\rbrack\;-\;{\mathrm{PaCO}}_2/\mathrm R\;-\;\mathrm{PaO}2\;$$

$$(\mathrm{PB}=\;760\mathrm{mmHg},\;{\mathrm P}_{\mathrm H2\mathrm O}=\;47\mathrm{mmHg},\;\mathrm R\;=\;0.8)$$

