**Methods:**

A prospective, randomized clinical trial will be performed in Hebei General Hospital. 106 patients undergoing elective surgery in prone position will be randomly divided into controlled group (group C) and individualized PEEP group (group I). Lung-protective ventilation with tidal volume of 6ml/kg predictive body weight (PBW) and positive end-expiratory pressure (PEEP) of 5 cm H_2_O will be applied to patients in group C. Patients in group I will receive the same tidal volume as described in group C plus individualized PEEP corresponding to the maximum dynamic compliance (Cdyn) in the titration method. Our primary endpoint is the prevalence of postoperative delirium based on the Confusion Assessment Method (CAM) until postoperative day 3. Secondary endpoints include the intraoperative rSO_2_, respiratory variables, arterial blood gases, lung ultrasound score (LUS), postoperative VAS score, and plasma concentrations of IL-6, IL-1β and neuron-specific enolase (NSE).

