### Discharge criteria

The discharge criteria are as follows: (1) baseline rSO2 < 60%; (2) the operation time > 4 h, (3) intraoperative blood loss > 800 ml; (4) interruption of study protocol.

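### IL-1β, IL-6 and NSE are called both plasma and serum, and their one post-treatment draw is fixed only to a calendar day: a precision cost on secondary outcomes, cheaply reduced

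*Protocol article*

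**What the plan says.** All references are to the Protocol article.

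- **Matrix.** In Outcome assessment the secondary outcomes include "plasma concentrations of interleukin (IL)-1β, IL-6, and NSE", and the Methods part of the Abstract also says plasma. Later in the same Outcome assessment paragraph the assay sentence reads "The serum concentrations of interleukin (IL)-1β, IL-6, and NSE will be determined by ELISA kits".
- **Timing.** "We will collect the blood samples 15 minutes before anesthesia induction (T_0_) and postoperative day 1". The first draw is fixed to the minute and the second only to a day. Elsewhere in the section, T1 to T4 are set in minutes from a defined event, and the delirium assessment has a clock window: "The researcher will assess POD once daily, between 6: 00 am to 8: 00 am".
- **Schedule.** Table 1 is not shown. Its legend defines T0 to T4 and gives no time for the day-1 draw.
- **Analysis.** Statistical methods compares continuous data with independent-samples t tests or Mann-Whitney U tests. Repeated-measures ANOVA is assigned to comparisons within a group. No between-group biomarker analysis that uses the T0 value is described.

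**The concern.** The Background hypothesis is that individualised PEEP prevents delirium by reducing inflammation and improving rSO2. IL-1β and IL-6 measure the inflammatory half of it, and each patient contributes one post-treatment value.

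If these markers change with time since surgery, two patients drawn at different hours of day 1 differ partly because of elapsed time. With one post-treatment sample, no individual course can be fitted, and the article does not mention recording the draw time. The scatter therefore goes into the error term. A difference that exists could be missed, and the null result could be read as evidence against the mechanism.

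The matrix is a separate matter. One paragraph gives the same three analytes two sample types, and a reader cannot tell which will be collected.

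**Working it through.** **Matrix.** The outcome list and the Abstract say plasma; the assay sentence says serum. Nothing says that both will be collected, or that one matrix is used at T0 and the other on day 1. The contradiction is one of description and can be settled only by naming a single matrix.

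**Timing.** The article gives no SD, effect or power for the biomarkers, so there is no figure of its own to reproduce. What follows is an illustration.

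Inputs from the article: 1:1 allocation; two-sided 0.05; 42 evaluable patients per arm; the 06:00-08:00 delirium window. The limit on duration, "the operation time > 4 h", bounds the length of the operation and not the hour at which it ends.

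Assumptions, none in the article: surgery ends uniformly between 10:00 and 18:00; the draw is independent of that and uniform over its window; the marker falls log-linearly with half-time h = 12 or 24 h; between-patient log SD s = 0.8.

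1. Range of hours since surgery. Any time on day 1: 24 − 18 = 6 h to 48 − 10 = 38 h. Draw at 06:00-08:00: 30 − 18 = 12 h to 32 − 10 = 22 h.
2. SD of hours since surgery, the sum of two independent uniform variables. Any time: √(8²/12 + 24²/12) = √53.3 = 7.30 h. Morning: √(8²/12 + 2²/12) = √5.67 = 2.38 h.
3. On the log scale, SD_t = SD × ln 2 / h. Relative rise in variance = SD_t² / s².
4. Power, if fixed timing gives 80%: Φ(2.80/√VR − 1.96), where VR is the variance ratio and 2.80 = 1.96 + 0.84. The number per arm cancels.

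| Draw | Half-time | SD_t (log) | Rise in variance | Power |
|---|---|---|---|---|
| Any time on day 1 | 12 h | 0.422 | 0.178/0.64 = 28% | 70% |
| Any time on day 1 | 24 h | 0.211 | 0.0445/0.64 = 7% | 77% |
| 06:00-08:00 | 12 h | 0.138 | 0.0189/0.64 = 3% | 79% |
| 06:00-08:00 | 24 h | 0.069 | 0.0047/0.64 = 0.7% | 80% |

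5. Sensitivity. With s = 0.5, any-time power is 57% (12 h) and 73% (24 h). With a 6 h half-time it is 30% (s = 0.5) to 49% (s = 0.8); with 48 h it is 78% to 79%.
6. Bias. In 20,000 simulated trials with no treatment effect, 42 per arm, any-time draws, h = 12 h and s = 0.5, the t test rejected in 5.15% of trials (nominal 5%; Monte Carlo standard error √(0.05 × 0.95/20,000) = 0.15%). Timing scatter that is the same in both arms leaves the type I error intact.

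**The case against.** The strongest reply is that this is a condensed article. A draw window for a secondary biomarker may stand in the full protocol or in the body of Table 1, which cannot be seen, and a day-1 draw is not wrong in itself. That stands: the missing window cannot be counted as an error. What remains is a suggestion, supported by the fact that the article does give times for its other assessments.

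The size is also assumed throughout, and draws spread evenly from midnight to midnight are an extreme case. If ward practice already means a morning draw, little is lost. This stands too.

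A morning draw is still tied to the calendar and leaves a 10 h range (12 to 22 h). True, but under the assumptions above that range costs about 3% or less in variance, and recorded hours allow adjustment for the rest.

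Three stronger readings are tempting, and the article supports none of them.

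- *That the biomarker comparison is biased.* Allocation is randomised and draw time is not tied to arm, so scatter is expected to be equal.
- *That plasma and serum will be mixed and the change in NSE made uninterpretable.* No text says that the matrices are mixed or switched. If one is used throughout, this is a wording error.
- *That the variance rises by 44% to 11%.* This follows from treating the 6 to 38 h range as one uniform variable (32/√12 = 9.24 h). End of surgery and draw time vary separately, which gives 7.30 h and 28% to 7%.

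**Conclusion.** The point holds as a low-cost improvement to secondary outcomes. The plasma and serum wording is a real internal contradiction, close to clerical on its own. The day-1 draw is loosely fixed and, as far as the article shows, would be analysed without adjustment.

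The cost is precision only: about 28% to 7% extra variance if draws fall at any hour of day 1, against about 3% to 0.7% with a 06:00-08:00 draw. These figures rest on the assumed end-of-surgery times, even spread of draws, half-time of 12 to 24 h and log SD of 0.8. The article supplies none of these, so the trial's place in the range is unknown. The primary delirium endpoint and the sample size are not affected.

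**What to change.** 1. **Matrix.** Name one matrix for both the T0 and day-1 samples and correct the other mentions in the Abstract and Outcome assessment. If the participants already recruited were all sampled in one matrix, keeping that one holds the series uniform.
2. **Draw time.** Take the day-1 sample at the existing 06:00-08:00 visit. Record the clock time of the draw and of the end of surgery.
3. **Analysis.** Compare groups on log-transformed day-1 values in a linear model with the log T0 value as covariate, in place of the unadjusted t or Mann-Whitney test for these three markers. Baseline adjustment multiplies the residual variance by about 1 − ρ², where ρ is the correlation between T0 and day-1 log values, which the article does not give. Add hours since end of surgery where recorded. A draw time may not exist for those already sampled, so keep the T0-adjusted model for all patients and report the hours-adjusted model beside it.

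Trial status reports 12 participants recruited at submission, so 106 − 12 = 94 draws could still have been standardised at that point. The cost is a sentence in the sampling schedule, two recorded times and a line in the analysis, with no extra sample or assay. The downside is slightly less freedom in when blood is drawn.

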**Table 1. Tab1:**
[figure not shown]
Standard Protocol Items: Recommendations for Interventional Trials (SPIRIT) Schedule for enrollment, interventions, and assessments. T0: after entering the operating room, T1: 5 minutes after starting mechanical ventilation in the supine position, T2: 60 minutes after turning over, and T3: 5 minutes after taking in the supine position, T4: after breathing air in PACU for 20 minute

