### Exclusion criteria

Patients who meet the following criteria will be excluded: (1) hypoalbuminemia or hypoxemia; (2) anemia; (3) chronic lung disease; (4) mental illness; (5) BMI ≥ 35 kg/m^2^; (6) contraindications to PEEP [16] (right heart failure, high intracranial pressure, or hypovolemic shock).

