### Interventions

Noninvasive blood pressure (NIBP), electrocardiogram, pulse oxygen saturation, bispectral index (BIS), body temperature, and rSO_2_ of patients in each group will be routinely monitored after entering the operating room. We will place two brain oxygen electrodes 4 cm from the forehead to the brow arch (one on the left and another on the right) to measure rSO_2_ by using near-infrared spectroscopy (NIRS). After placement of monitors, radial artery puncture and catheterization will be performed under local anesthesia, allowing intermittent blood gas analyses and continuous hemodynamic monitoring.

Patients will receive intravenous propofol (2 mg/kg), sufentanil (0.3 µg/kg), and cisatracurium (0.15 mg/kg) for anesthesia induction and tracheal intubation after preoxygenated (inspired oxygen fraction of 0.8) for three minutes. During surgery, sevoflurane inhalation and continuous intravenous remifentanil and propofol infusion will be employed to maintain BIS between 40 and 60. Intermittent administration of cis-atracurium will provide sufficient muscle relaxation. Vasoactive drugs will be used to maintain mean arterial pressure (MAP) and heart rate within ± 20% of the baseline. The core temperature will be maintained above 36.0 ℃ by using a forced air warming system. Subsequently, when patients can respond to verbal commands, they will undergo extubating procedures and be transferred to the postanesthesia care unit (PACU) until fully awake. Patients will routinely receive intravenous patient-controlled analgesia (PCIA) to control postoperative pain.

Mechanical ventilation will be maintained with V_T_ 6 ml/kg PBW, FIO_2_ of 50%, and I: E of 1:2 with PCV-VG mode. After the prone position is established, both groups will receive the recruitment maneuver by squeezing a reservoir bag up to 30–40 cm H_2_O for 15–20 s. The initial respiratory rate will be set to 12 breaths per minute and P_ET_CO_2_ is maintained in the range of 40 ± 5 mm Hg by adjusting the respiration rate.

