The patients in both groups will receive the PEEP of 5 cm H_2_O after endotracheal intubation, and this PEEP level will be maintained throughout the whole procedure in the group C. After the prone position is set up, patients in Group I will receive optimal individualized PEEP identified by an incremental PEEP titration protocol (Fig. 2). The PEEP titration method is as follows: each PEEP level (4, 6, 8, 10, 12, 14, 16 cm H_2_O) will be maintained for 60 s. Meanwhile, we will record the Cdyn at each PEEP level. We will select the optimal PEEP level based on the maximum Cdyn and maintain it throughout the whole study period. If circulatory instability occurs during PEEP titration, intravenous infusion of noradrenaline will be used to maintain MAP ≥ 55mmHg.

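### The only postoperative blood gas (T4, on room air) has no like-for-like room-air baseline, which costs precision and interpretability for a secondary outcome but not validity

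*Protocol article*

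**What the plan says.** The Outcome assessment section of the protocol article lists arterial blood gases among the secondary outcomes and gives the schedule: "Arterial blood gases will be measured at T_1_ to T_4_ (after breathing air in PACU for 20 minutes". No gas is listed at T0. Table 1 defines the first sampling point: "T1: 5 minutes after starting mechanical ventilation in the supine position". The Interventions section fixes the conditions at that time: "Mechanical ventilation will be maintained with V_T_ 6 ml/kg PBW, FIO_2_ of 50%, and I: E of 1:2 with PCV-VG mode" and "The patients in both groups will receive the PEEP of 5 cm H_2_O after endotracheal intubation". The arms part only later: "After the prone position is set up, patients in Group I will receive optimal individualized PEEP identified by an incremental PEEP titration protocol".

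Interventions also describes the arterial line ahead of preoxygenation and induction: "radial artery puncture and catheterization will be performed under local anesthesia, allowing intermittent blood gas analyses". Preoxygenation, at an inspired fraction of 0.8, lasts three minutes. For the biomarkers, Outcome assessment states: "We will collect the blood samples 15 minutes before anesthesia induction (T_0_) and postoperative day 1". PaO2/FiO2, A-aDO2 and Qs/Qt are recorded at T1 to T3 only.

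Statistical methods compares continuous data between groups by independent-samples t test or Mann-Whitney test. Repeated measures ANOVA is named for within-group comparisons only. No baseline-adjusted analysis is stated.

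**The concern.** At T2 the arms are on different PEEP. The chosen level is to be kept for the rest of the study period, so the same presumably holds at T3. A difference in gases at those times may reflect only the pressure being applied. T4 is the one gas taken after the intervention with both arms breathing air without the ventilator, so among the gases it best shows whether an oxygenation benefit outlasts extubation. It has no counterpart from before surgery. By contrast, rSO2 and the biomarkers each have a pre-induction value.

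Two things are lost. The change in room-air PaO2 from before to after surgery cannot be described for any patient. And an unadjusted test leaves all stable between-patient variation in PaO2 in the error term, so a modest lasting difference is harder to detect than it need be.

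**Working it through.** The plan gives no figure on this point, so there is none to reproduce. The check sets out the schedule and then sizes the gain in precision.

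**1. Conditions at each gas** (Table 1, Interventions, Outcome assessment)
- T0: no gas listed.
- T1: supine, ventilated, FiO2 50%, PEEP 5 cm H2O in both arms.
- T2: prone, ventilated, FiO2 50%, PEEP differs by arm.
- T3: supine again, ventilated, FiO2 50%, PEEP presumably still as assigned.
- T4: PACU, after 20 minutes on air.

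No earlier gas matches T4, so a like-for-like change is not available. T1 does precede the protocol's treatment difference in every patient.

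**2. Is a room-air T0 gas feasible?** The line is described before the three-minute preoxygenation, and the biomarker blood is drawn 15 minutes before induction. A gas on air in that window looks feasible. Two limits apply: the biomarker sample is not said to be arterial, and the order of line placement and biomarker draw is inferred from the narrative.

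**3. Gain over no adjustment.** With ANCOVA, the variance of the T4 comparison is multiplied by 1 − r², where r is the correlation between the covariate and T4 PaO2. The documents give no r, so the values are assumptions.
- r = 0.4: 1 − 0.16 = 0.84, a 16% reduction, equivalent to 1/0.84 = 1.19 times the patients
- r = 0.5: 1 − 0.25 = 0.75, a 25% reduction, 1/0.75 = 1.33 times
- r = 0.7: 1 − 0.49 = 0.51, a 49% reduction, 1/0.51 = 1.96 times

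The detectable difference in SD units, at two-sided 5%, 80% power and the 42 per group of Sample size calculation, is (1.960 + 0.842) × √(2/42) × √(1 − r²). This gives 0.61 unadjusted, 0.53 at r = 0.5 and 0.44 at r = 0.7.

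**4. T1 as covariate.** A covariate must precede the treatment difference and correlate with the outcome. It need not share the outcome's FiO2 or scale. In 4,000 simulated trials for each of r = 0.3, 0.5 and 0.7, with 42 per arm and the covariate on a different scale, the adjusted estimate was unbiased (mean error at most 0.006 SD). Type I error was 0.045 to 0.050.

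**5. Gain of T0 over T1.** The sample-size ratio is (1 − r₁²)/(1 − r₀²), with r₁ for T1 and r₀ for T0.
- r₁ = 0.3, r₀ = 0.5: 0.91/0.75 = 1.21
- r₁ = 0.3, r₀ = 0.7: 0.91/0.51 = 1.78
- r₁ = r₀: 1.00, no gain
- r₁ = 0.5, r₀ = 0.4: 0.75/0.84 = 0.89, T0 alone is worse

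**The case against.** The strongest objection is that nothing here is an error. The endpoint is secondary, the protocol promises no room-air change or baseline-adjusted T4 analysis that the schedule would defeat, and choice of covariate can be left to an analysis plan that is not shown. Persistence of a lung effect is also assessed by lung ultrasound at T1 and T4, scored by an anesthetist unaware of allocation. The assumed correlations have no source in the documents. All of this stands, and it keeps the point to a cheap design improvement.

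Three stronger readings might be inferred, and the documents do not support them.
- *That T4 cannot be adjusted for baseline at all.* T1 is a gas in every patient before the arms diverge and can be the covariate. What it cannot supply is a like-for-like change score.
- *That chance baseline imbalance is an added hazard.* With an assumed SD of 8 to 12 mmHg, 1.96 × SD × √(2/42) gives chance arm differences of up to 3.4 to 5.1 mmHg in 95% of randomizations. This is ordinary sampling variation, already in the standard error of the t test. The false-positive rate stays at its nominal 5%.
- *That the exclusion for "hypoalbuminemia or hypoxemia" lacks an arterial value because of this gap.* Patients are enrolled the day before surgery and the line is placed in the operating room, so a T0 gas would come too late to inform eligibility.

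There is a fair case for T0 over T1. T0 and T4 would share air and spontaneous breathing, so a higher correlation is plausible. T1 also follows induction by an anesthesiologist who knows the allocation. Neither argument proves that r₀ exceeds r₁.

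**Conclusion.** The point holds as a minor one. T4 has no room-air counterpart, so the pre-to-post change on air cannot be computed, and the stated between-arm test uses no baseline at all. The comparison of randomized arms at T4 remains valid.

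Against no adjustment, a baseline covariate would cut the variance by 16% to 49%, assuming r of 0.4 to 0.7. Much of that may be available from T1 alone. The further gain from T0 ranges from nothing, if the two correlate equally with T4, to the equivalent of 21% to 78% more patients for this outcome, if r is 0.3 for T1 and 0.5 to 0.7 for T0. The schedule facts rest on the text of Outcome assessment, because the body of Table 1 is not shown.

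**What to change.** - **Schedule:** add one arterial gas at T0, on room air, from the radial line once placed and before preoxygenation. State explicitly that it precedes any supplemental oxygen.
- **Analysis:** compare T4 PaO2 between arms by ANCOVA with the T0 value as covariate, in place of the unadjusted test.
- **Patients without T0:** use T1 as covariate. One workable form is a single model with T1 for everyone, and T0 with a missing-value indicator. Lack of T0 then depends on enrolment date and not on arm. Trial status reports 12 of the planned 106 patients recruited at submission.
- **If T0 is not added:** use T1 as the covariate throughout, at no cost, and report T4 as a between-arm comparison only, without a change from baseline.

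The cost is one gas analysis per patient, at most 106 − 12 = 94 counted from submission, plus one schedule entry. No extra puncture is needed if the line is in place as described.

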## Background

Postoperative delirium, a serious postoperative neurological complication, characterized by acute and fluctuating changes in consciousness and attention, can increase morbidity and mortality in patients over 60 years of age [1]. Due to different types of surgery, POD in elderly patients has been reported to occur in 10%-60% [2].

Mechanical ventilation could induce proinflammatory response and ventilator-induced lung injury (VILI), which may increase the incidence of POD [3, 4]. The prone position is commonly used during percutaneous nephrolithotripsy or spine surgery to provide a fine condition for the operation. However, this non-physiological position can cause increased peak airway pressure (P_peak_), decreased Cdyn, thus aggravating lung injury [5, 6]. In addition, perioperative cerebral desaturation may increase the risk of POD among different types of surgery [7, 8]. Significantly, cerebral desaturation commonly occurs in elderly surgical patients undergoing prone position [9]. Thus, patients undergoing prone position may be at high risk of POD owing to decreased rSO_2_ and VILI-induced inflammatory response. Recent research suggested that intraoperative lung-protective ventilation might help prevent POD by inhibiting inflammation and improving rSO_2 _[4].

Intraoperative lung-protective ventilation strategies, including low tidal volumes (V_T_), PEEP, and recruitment maneuvers (RM), have been proved to alleviate lung injury and prevent POD [4, 10]. Our previous studies have shown that individualized PEEP combined with pressure-controlled ventilation-volume guaranteed (PCV-VG) mode could mitigate lung damage, and lead to favorable oxygenation in patients undergoing thoracoscopic surgery and laparoscopic surgery [11, 12]. Recent studies demonstrated that the application of PEEP could induce significant increases in rSO_2_ [4, 13]. Whether individualized PEEP could prevent POD is not clear. Hence, we hypothesized that individualized PEEP can prevent POD by reducing inflammatory response and improving rSO_2_.

Based on the above studies, our aim is to explore the neuroprotective effect of individualized PEEP among elderly patients undergoing mechanical ventilation in prone position. This trial will replenish further clinical evidence of employing intraoperative individualized PEEP to prevent POD.

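### At T2 and T3, PEEP, Cdyn, Ppeak and Pmean are partly determined by the intervention, so they are weak evidence of lung benefit, and Ppeak can rise in Group I while inflation pressure falls

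*Protocol article*

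**What the plan says.** All references are to the protocol article.

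- **Outcome status.** Outcome assessment states: "The secondary outcomes will include perioperative rSO_2_ measurement, arterial blood gases, respiratory variables". The respiratory list then names "Respiratory variables including P_ET_CO_2_, PEEP, P_peak_, mean airway pressure (P_mean_), Cdyn" and gas-exchange indices, recorded at T1 to T3.
- **Treatment contrast.** Interventions states: "The patients in both groups will receive the PEEP of 5 cm H_2_O after endotracheal intubation". For the control arm, "this PEEP level will be maintained throughout the whole procedure in the group C". In Group I, after turning prone, "each PEEP level (4, 6, 8, 10, 12, 14, 16 cm H_2_O) will be maintained for 60 s", and then "We will select the optimal PEEP level based on the maximum Cdyn and maintain it throughout the whole study period".
- **Settings common to both arms.** Interventions sets tidal volume at 6 ml/kg predicted body weight, I:E at 1:2 and PCV-VG mode. Respiratory rate is adjusted to hold PETCO2 at 40 ± 5 mm Hg.
- **Timing.** T1 is supine and precedes titration. T2 is 60 minutes after turning prone. T3 is supine again.
- **Analysis.** Statistical methods gives t tests or Mann-Whitney tests for continuous data. Repeated measures ANOVA is reserved for comparisons within a group.
- **Rationale.** Background says of the prone position that "this non-physiological position can cause increased peak airway pressure (P_peak_), decreased Cdyn, thus aggravating lung injury".

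**The concern.** The trial's reasoning runs from less ventilator-induced lung injury to less inflammation and so to less delirium. A reader will look to the respiratory outcomes for the first link. Several of them are tied to the intervention by definition or by the selection rule:

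- **PEEP** at T2 and T3 is the treatment itself. Testing it between arms checks delivery.
- **Cdyn** is the criterion by which Group I's PEEP is picked, and nothing is picked in Group C. A Cdyn advantage at T2 largely reflects that choice.
- **PETCO2** is steered to one target in both arms, so a null result is expected and says little.
- **Ppeak and Pmean** are measured from zero and so include the PEEP. They mix the assigned level with the pressure needed to inflate the lung.

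At stake is how the mechanistic secondary results are read. A Cdyn gain could be presented as independent support, or a Ppeak rise as a sign of a worse lung, when neither follows.

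**Working it through.** The protocol gives no value for Ppeak, Pmean, Cdyn or the PEEP expected in Group I, so there is no stated figure to reproduce. The numbers below are illustrations.

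**Inputs from the protocol:** PEEP 5 in Group C; candidate levels 4 to 16 in steps of 2 in Group I; tidal volume (VT) 6 ml/kg; I:E 1:2.

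**Assumed:** predicted body weight 60 kg, so VT = 6 × 60 = 360 ml; Cdyn 30 ml/cm H2O at PEEP 5; a fractional Cdyn gain *g* at the selected PEEP *P*.

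**Formulas** (pressure-controlled breath, approximately square pressure wave):
- Cdyn = VT / (Ppeak − PEEP), so Ppeak = PEEP + VT/Cdyn
- Pmean ≈ PEEP + (Ppeak − PEEP)/3 at I:E 1:2
- With D = VT/Cdyn at PEEP 5, the Ppeak difference (I − C) is (P − 5) − D·g/(1 + g)

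**Step 1, one worked case** (P = 10, g = 20%, so Cdyn = 36):

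| | Group C | Group I |
|---|---|---|
| Ppeak − PEEP | 360/30 = 12 | 360/36 = 10 |
| Ppeak | 5 + 12 = 17 | 10 + 10 = 20 |
| Pmean | 5 + 12/3 = 9.0 | 10 + 10/3 = 13.3 |

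Ppeak is 3 cm H2O higher in Group I while the pressure above PEEP is 2 cm H2O lower.

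**Step 2, Cdyn needed for equal Ppeak.** Setting Ppeak to 17 gives Cdyn = 360/(17 − P):

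| Selected PEEP | Cdyn needed | Rise from 30 | Rise needed if Cdyn at PEEP 5 is 25 to 40 |
|---|---|---|---|
| 6 | 360/11 = 32.7 | 9% | 7% to 12% |
| 8 | 360/9 = 40 | 33% | 26% to 50% |
| 10 | 360/7 = 51.4 | 71% | 53% to 125% |
| 12 | 360/5 = 72 | 140% | 95% to 350% |

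At a selected PEEP of 4 no rise is needed: Ppeak is below 17 for any Cdyn above 360/13 = 27.7.

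**Step 3, range.** Body weight 50, 60, 70 kg; Cdyn at PEEP 5 of 25, 30, 35, 40; gain 10%, 20%, 30%. That is 36 combinations per PEEP level.

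| Selected PEEP | Ppeak higher in Group I | Pmean higher in Group I |
|---|---|---|
| 4 | 0 of 36 | 0 of 36 |
| 6 | 6 of 36 | 33 of 36 |
| 8 to 16 | 177 of 180 | 180 of 180 |

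These are counts over a grid of assumptions, not probabilities. They show that the sign of the Ppeak contrast turns mainly on which PEEP is selected. Every scenario has a Cdyn gain, so Ppeak − PEEP falls in all of them.

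**Step 4, Cdyn.** The selection rule favours a higher Cdyn in Group I but does not guarantee it. The level of 5 used in Group C is not among the levels tested, T2 comes well after titration, and at T3 a PEEP chosen prone is applied supine.

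**The case against.** Much can be said for the plan.

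- A higher Ppeak under a higher PEEP is a real consequence of assignment, so the randomised contrast is a valid total effect. It also bears on safety, since Safety evaluation lists pneumothorax as an adverse event. **This stands**, and Ppeak and Pmean should be kept.
- With tidal volume set per kilogram, Cdyn already carries the PEEP-corrected information, because Ppeak − PEEP = VT/Cdyn. **This stands too.** It means Ppeak − PEEP is no independent replacement: maximising Cdyn at fixed VT is the same as minimising it.
- The stated hypothesis concerns inflammation and rSO2, which are measured directly. **This stands** and limits the damage.
- The list is introduced as non-exhaustive, and baseline adjustment is often left to an analysis plan. **This stands in part.** A fuller document may add Ppeak − PEEP or a covariate. But the article does class PEEP and the titration target as secondary outcomes, and it does name the between-group tests.

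A reader might go further and infer that all these comparisons are fixed by design, or that the trial will score a real improvement as harm. The document supports neither. T1 precedes titration with both arms on PEEP 5, Ppeak can fall at a selected PEEP of 4 or 6, and a Cdyn gain is not assured. The Background sentence on Ppeak describes an effect of position, and no section says that a higher Ppeak in Group I will be read as harm.

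**Conclusion.** The point holds in a limited form. At T2 and T3, but not T1, PEEP is set by assignment, Cdyn is favoured by the selection rule, and Ppeak and Pmean contain the assigned PEEP. These secondary comparisons are therefore partly determined by the intervention and cannot serve as independent evidence that the lung is better or worse off.

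The size depends wholly on assumed body weight, compliance and selected PEEP. Under the illustrated values Ppeak goes from 17 to 20 while inflation pressure goes from 12 to 10. If most patients are titrated to 8 or above, a higher Ppeak in Group I is likely across the range examined; at 4 or 6 it mostly is not. The delirium endpoint is untouched. This is a matter of labelling and interpretation, and it is cheap to settle before the data are analysed.

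**What to change.** In Outcome assessment and Statistical methods:

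1. Label PEEP, PETCO2 and Cdyn at T2 and T3 as delivery (process) checks, not as independent evidence of lung benefit. Keep recording PETCO2, which the dead-space formula needs.
2. Keep Ppeak and Pmean as descriptors of total airway pressure, relevant to safety. Report Ppeak − PEEP beside them, stating that it is linked to the Cdyn target and is not independent evidence.
3. Compare the T2 and T3 respiratory variables with adjustment for the T1 value (for example ANCOVA) in place of unadjusted t tests. T1 is a usable baseline because both arms are then on PEEP 5. The adjustment gains precision and deals with chance imbalance; it does not remove PEEP from Ppeak, so items 1 and 2 are still needed.
4. Rest claims of lung benefit on the gas exchange, lung ultrasound and biomarker outcomes already planned. The blood gases and ultrasound at T4 are taken breathing air in the PACU, and the biomarkers on postoperative day 1, so none of these is measured under the assigned PEEP.

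The cost is one subtraction on recorded values, some relabelling and one covariate. No new data are needed and patient care does not change. The downside is fewer variables on which to claim a benefit.
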